# Collaborative treatment of late-life depression in primary care (GermanIMPACT): study protocol of a cluster-randomized controlled trial

**DOI:** 10.1186/1745-6215-15-351

**Published:** 2014-09-06

**Keywords:** Collaborative care, Late-life depression, Stepped care

## Abstract

**Background:**

Depression is not a normal side effect of aging, however it is one of the most prevalent mental health issues in later life, imposing a tremendous burden on patients, their families, and the healthcare system. We describe the experimental implementation of a collaborative, stepped-care model for the treatment of late-life depression (GermanIMPACT trial) in the German primary care context. GermanIMPACT was developed as an adaptation of a successful and widely used American model. The aim of the study is to evaluate the model’s applicability to the German primary care setting and its cost-effectiveness.

**Methods/Design:**

The study will be conducted as a cluster-randomized controlled trial comparing the development of depressive symptoms in primary care patients who either receive treatment as usual (control arm) or treatment according to the GermanIMPACT model (intervention arm). In two German cities (Freiburg and Hamburg), a total of 60 general practice offices will be selected and randomized. Each general practice office will be asked to enroll five patients into the trial who are 60 years of age or older and who show moderate depressive symptoms in the scope of a diagnosed depressive episode, recurrent depressive disorder, or dysthymia. General practices in the control arm will provide treatment as usual; general practices in the intervention arm will work closely with a specially trained care manager and a supervising mental health specialist. Evidence-based elements of the treatment plan manual include patient education, identification and integration of positive activities into the daily routine, relapse prevention, and training of problem-solving techniques as needed. The intervention period per patient will be one year. Data will be collected at baseline, 6, and 12 months. Primary outcome is the patient-reported change of depressive symptoms (Patient Health Questionnaire, PHQ-9). Secondary outcomes include measures of quality of life, anxiety, depression-related behavior, problem-solving skills, resilience, and an overall economic evaluation of the program.

**Discussion:**

The GermanIMPACT trial will provide evidence about the effectiveness, feasibility, and cost-effectiveness of collaborative stepped care in treating late-life depression in German primary care. Positive results will be a first step toward integrating specialized depression care managers into the primary care setting.

**Trial registration:**

German Clinical Trials Register: DRKS00003589 (September 2012).

## Background

### Late-life depression

Depression, including major depression and less severe forms with clinically relevant depressive symptoms, is one of the most prevalent mental disorders in older adults and is considered a serious public health problem. International studies show that major depression affects up to 9.3% of individuals aged 75 years or older; less severe forms occur with a frequency of up to 37.4% [1, 2]. Depression, especially in combination with morbidity, disability, and social disconnectedness, is one of the key risk factors for suicide in later life [3]. To date, there are only a few studies on incidence rates of depression in older adults. Although findings vary considerably depending on diagnostic criteria and study method, some results indicate that incident rates in people between 60 and 70 years of age are equal to or lower than those found in the younger age groups [4]. A recent epidemiological field study suggested that the incidence and prevalence of depression rise again upon reaching the age of 70, and that cohort effects may further aggravate this phenomenon [5].

In primary care, the diagnostic situation is complicated by the fact that late-life depression often manifests as a mix of somatic conditions and cognitive impairment [6, 7] and often does not present with complaints regarding mood [4]. Hence, it can be assumed that a high number of older adults suffering from depression remain undiagnosed [4, 8].

Moreover, many people suffering from depression are poorly educated about the treatability of mood disorders. Yet another factor to be taken into account is the stigma associated with mental illness, especially for the older generation and within the German historical context. As a result of self-stigmatization, many older adults may consider depression a sensitive topic and be less likely to report their symptoms or consult a psychiatrist or psychotherapist [9]. Besides these psychological factors, the lack of sufficient regional mental health services and reduced mobility in older age may contribute to the low number of older patients treated by mental health specialists. While older adults suffering from major depression in Germany tend to see their general practitioner twice as often as they would without depression, they only have an average of 0.7 consultations with a psychiatrist or 1.3 consultations with a psychotherapist over a period of 12 months [10]. Given a recommended minimum of four psychiatric consultations over the course of 12 months for successful treatment, this means that only 17.5% of older patients receive a depression-specific intervention.

### Collaborative depression care

Cross-national research provides ample evidence for the advantage of structured collaborative depression care (CDC) approaches over traditional therapeutic interventions in primary care [11, 12]. Translational research has encouraged widespread implementation of CDC in diverse practice settings [13]. In the United States, several CDC programs have been evaluated and applied in practice for more than a decade. Although more research is needed regarding the cost-effectiveness of the collaborative care approach, recent studies are yielding promising results [14].

One core feature of CDC in primary care is low-threshold case management provided by trained nursing staff or counseling professions, such as social workers [12, 15]. In addition, the involvement of a supervising mental health specialist (MHS) has proven to be a crucial and discretely effective element in the interdisciplinary treatment of depression [13, 16–18].

In 2002, Unützer *et al*. [19] conducted an internationally recognized and frequently cited randomized controlled trial on their CDC model (IMPACT: Improving Mood - Promoting Access to Collaborative Treatment). Since then, the model has successfully been applied in many American primary care institutions. The IMPACT treatment plan includes a care manager (CM) and a supervising MHS. It is designed as a stepped-care model in which the intervention is tailored to the patients’ individual needs, allowing for optimal treatment results and minimal costs. Moreover, IMPACT has proven feasible and effective not only in the treatment of depression, but of other psychiatric conditions as well, namely anxiety and panic disorders [20].

### IMPACT: key agents and core elements

The following three professional key agents (providers) form the IMPACT treatment triad are depicted in Figure 1.

**Figure 1 Fig1:**
[figure not shown]
**IMPACT treatment triad (solid line: regular contact; broken line: contact as needed).**

The first agent in the interdisciplinary triad is the patient’s primary care provider, typically a general practitioner (GP) in an individual office for the German context. The GP diagnoses or confirms the diagnosis of depression and initiates treatment. He or she communicates with the CM on a regular basis in order to exchange information about the patient’s progress and to discuss adequate treatment adaptation as needed.

As central figure in the intervention process, a trained nurse or social worker in the role of the CM supports the treatment initiated by the GP by means of proactive and continuous follow-up with the patient. Intervention techniques provided by the CM typically include patient education (regarding symptoms, course of disorder, medication, side effects and so on), identification and integration of positive activities into the daily routine, relapse prevention, and training in problem-solving techniques as needed. These therapeutic elements have been proven to be effective in the treatment of depression and are recommended on high evidence levels by international clinical guidelines [21] (based on the procedure used by the Center of Evidence Based Medicine, all therapeutic elements hold the highest evidence degree [22]).

The third agent in the IMPACT treatment triad is a consulting and supervising MHS, that is, a psychiatrist or psychotherapist. The MHS supervises the intervention through regular meetings with the CM and provides professional guidance in difficult cases. He or she can be contacted by the GP regarding medical treatment options and is available in case of an emergency. In exceptional cases and after prior consultation with the CM, the GP can refer a patient directly to the MHS, for example, if the patient does not respond to the treatment.

Patient education and counseling provided by the CM focuses on the modification of cognitive appraisal and behavior, a powerful tool in the psychotherapeutic treatment of depression. Problem-solving techniques (PST) as an element of cognitive behavioral therapy are integrated into the treatment plan according to the patient’s individual symptom remission or lack thereof. The method has proven successful in numerous depression trials and can easily be acquired by a wide variety of professionals working in the healthcare field [23].

### Study aim and objectives

In recent years, clinical researchers around the globe have shown an increased interest in the applicability of collaborative care models, such as IMPACT, in different cultural settings and with different patient populations [15, 24]. In Europe, the model has been studied extensively in the Netherlands and the United Kingdom [25–30]. Until now, there have been only a few studies in Germany. Existing studies have not involved an MHS as a core intervention component, for instance, in the form of psychiatric supervision [31, 32].

The GermanIMPACT trial aims at broadening the scope of generalizability and the body of evidence for the adaptability of the IMPACT model to the German primary care context. Mental health research indicates that sustainable intervention programs need to be adapted carefully to existing systems and practices [13]. Thus, one of the key challenges was to create a concept compatible with the specific context of primary care in Germany without affecting the fidelity of the model, especially the core philosophy and elements.

Positive results in terms of symptom remission in collaboratively treated depressive patients will reinforce the cross-national applicability of the IMPACT core concept. In addition, such results will underline the impact of behavioral interventions in depression care and their successful implementation outside the specialized setting of high-frequency psychotherapy. The results will serve the goal of improving the treatment of late-life depression by paving the way for evidence-based intervention models in primary care. Proving the efficacy of the collaborative approach and its cost-effectiveness will be the first step towards its implementation into the German healthcare system.

## Methods/Design

### Setting

GermanIMPACT is a cooperation of the university medical centers of Freiburg and Hamburg-Eppendorf, Germany. Both centers serve as study sites, each with 30 participating GPs. The GPs will be recruited through the centers’ respective general practice departments. The Freiburg medical center is the coordinating center and is in charge of the management of data collected in Freiburg. The Hamburg medical center is responsible for the statistical analysis, assessments related to health economics, and the management of data collected in Hamburg. At each site, two CMs with a background in nursing are appointed and trained. Their offices are based at the university medical centers. This allows for easy access to the supervising MHSs who are part of the GermanIMPACT team and clinical staff at the medical centers.

Due to the geographic dispersion of German GP offices and the lack of additional practice space, most follow-up contacts will be conducted over the telephone. Research has shown that telephone interventions are a common and effective tool in depression care [12, 17]. Mandatory regular visits requiring traveling on the part of the patients would most likely be perceived as cumbersome and lead to dropouts. Additional face-to-face sessions will be scheduled only if considered necessary by the treatment triad.

### Sample size

The remission of depressive symptoms as measured by the Patient Health Questionnaire PHQ-9 at 12 months’ follow-up will be the primary outcome measure of the study. A randomized controlled trial investigating the effectiveness of the IMPACT program in the United States yielded a remission rate of 25.0% in the intervention group and 8.3% in the control group [19]. Assuming these remission rates in our trial along with a conventional value for the type I error rate (α = 0.05), a two-sided test on inequality of proportions requires 85 patients per arm (170 in total) to detect this effect with a power of 0.8 (type II error rate β = 0.2). Calculations were done with STATA 12.1 [33]. However, in order to account for the hierarchical structure of the collected data due to the cluster-randomized design, it must be considered that patients treated by the same GP are likely to be more similar in terms of treatment response than patients treated by different GPs. Assuming a fixed number of included GPs (30 per arm, 60 in total) and an amount of variance in the outcome explained by differences between physicians rather than between patients (intraclass correlation coefficient of 10%), the factor of the necessary increase in sample size (so-called ‘design effect’) due to the clustered design yields 1.46, increasing the required sample size to a total of 250 patients. This is the number needed for an appropriately powered per-protocol analysis (only completers are analyzed). To compensate for a conservatively estimated 15% loss to follow-up [19, 31], each participating GP will be instructed to include 5 patients in the study, amounting to a total of 300 patients allocated to the trial (150 per arm). The primary analysis will be performed in the intention-to-treat population, that is, all randomized patients will be included. In the intention-to-treat analysis, the higher number of patients is likely to be compensated for by a potential dilution of treatment effects, so that the power will be approximately the same as described for the per-protocol analysis.

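### The design effect of 1.46 and the 250 required completers do not follow from the stated 60 GPs and ICC of 10%; the error is conservative, and the target of 300 can stand

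*Protocol article*

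**What the plan says.** Everything at issue stands in the Sample size section of the protocol article.

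- **Effect:** the earlier US trial "yielded a remission rate of 25.0% in the intervention group and 8.3% in the control group", and these rates are assumed here.
- **Unclustered size:** "a two-sided test on inequality of proportions requires 85 patients per arm (170 in total"). The section gives this for 80% power at α = 0.05.
- **Clustering inputs:** "Assuming a fixed number of included GPs (30 per arm, 60 in total"), and an "intraclass correlation coefficient of 10" per cent.
- **Result:** the design effect "due to the clustered design yields 1.46, increasing the required sample size to a total of 250 patients". The section says this number is for an analysis of completers.
- **Recruitment:** allowing for 15% loss, "each participating GP will be instructed to include 5 patients in the study", which makes 300 patients.

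The section does not give the cluster size behind the 1.46 and does not mention unequal cluster sizes. It adds that power in the intention-to-treat analysis should be about the same, because dilution of the effect would offset the larger number of patients.

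**The concern.** The section prints both the inputs and the result of the clustering step, so a reader can check it, and the two do not agree. For a fixed ICC the design effect depends only on how many analysed patients each GP contributes. The value 1.46 requires clusters larger than any the plan foresees.

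What is at stake is the accuracy of the trial's main sizing statement. The design effect and the required number of completers are both misstated. The power claim attached to them is also wrong for the number of patients expected to complete, and the section carries that claim over to the intention-to-treat analysis, which is the primary one. This is not a detail that an article leaves to a fuller document, because the disagreement is between figures that are printed.

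**Working it through.** **Inputs** (all from the Sample size section): remission 25.0% and 8.3%; two-sided α = 0.05; power 0.80; n = 85 per arm before clustering; k = 30 GPs per arm, 60 in total; ICC ρ = 0.10; 15% loss; 5 patients per GP, 300 enrolled.

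**Step 1. The unclustered size.** Two-sided Fisher exact power is 0.794 at 84 per arm and 0.800 at 85, so the stated 85 reproduces. The section does not name the formula. The pooled normal formula gives 77 per arm and the continuity-corrected one 89.

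**Step 2. The cluster size that 1.46 implies.** For equal clusters of m analysed patients, DE = 1 + (m − 1)ρ. Hence m = 1 + (1.46 − 1)/0.10 = 5.6. By comparison, 300/60 = 5 are to be enrolled per GP, and 250/60 = 4.17 would complete. The plan's own multiplication is consistent with 250 after rounding up (170 × 1.46 = 248.2), so the fault lies in the design effect itself.

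**Step 3. The design effect from the stated inputs.** With the number of GPs fixed, the cluster size depends on the answer. So N = n[1 + (N/k − 1)ρ] per arm is solved for N:

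N = n(1 − ρ)/(1 − nρ/k) = 85 × 0.90/(1 − 8.5/30) = 76.5/0.7167 = 106.7

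That is 107 per arm and 214 in total, with m = 3.56 and DE = 1.26. Other readings of the cluster size give:

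| Patients per GP | DE | 170 × DE |
|---|---|---|
| 170/60 = 2.83 | 1.18 | 201 |
| 3.56 (solved for 60 GPs) | 1.26 | 214 |
| 250/60 = 4.17 | 1.32 | 224 |
| 255/60 = 4.25 | 1.33 | 225 |
| 5 (no loss at all) | 1.40 | 238 |

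None reaches 1.46 or 250. The stated 250 is 17% above 214 (250/214 = 1.17) and 5% above 238 (250/238 = 1.05).

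**Step 4. Power the design delivers.** Expected completers are 300 × 0.85 = 255, so m = 4.25 and DE = 1 + 3.25 × 0.10 = 1.325. The effective size is 255/1.325 = 192, or 96 per arm. Power is then 0.856 by Fisher's exact test, 0.837 with the continuity-corrected formula and 0.881 with the pooled formula.

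At exactly 250 completers (DE 1.317, about 95 effective per arm) the same three give 0.85, 0.83 and 0.88. A beta-binomial simulation of 60 GPs with a cluster-robust test gave 0.88 at 250 completers, with a type I error rate of about 0.05.

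**Step 5. The loss step.** 250/0.85 = 294.1, which 300 covers, so this step is sound. On the corrected figure, 214/0.85 = 251.8, or 252 enrolled. That is 4.2 per GP, which rounds up to 5 whole patients and again to 300.

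**Possible source.** Dividing the two-arm total by the GPs of one arm gives 170/30 = 5.67, DE = 1.467 and 170 × 1.467 = 249.3. This comes close to both printed figures, but 1.467 becomes 1.46 only by truncation, and the document does not say that this was done.

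**The case against.** The strongest reply is that nothing in the design changes. The corrected requirement still leads to 5 patients per GP and 300 in total, and 250 completers remain enough for 80% power under the stated assumptions. That stands, and it limits the point to a correction of stated figures.

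A second reply is that 214 and 0.86 look more exact than they are. This also stands in part. Both rest on the stated 85 per arm and on equal clusters. Starting from 77 or 89 per arm, the total for 60 GPs is 188 or 228. With 89 per arm and a full 5 per GP one does reach 178 × 1.40 = 249, but the section states 85, not 89, and a design effect of 1.46, not 1.40. The planned primary analysis is also a mixed-effects logistic model in the intention-to-treat sample, not Fisher's test on an effective sample size.

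A third reply is that 1.46 may contain a tacit allowance for unequal clusters. It cannot under this plan. With DE = 1 + [(1 + CV²)m − 1]ρ at m = 4.17, reaching 1.46 needs a coefficient of variation of about 0.59. If no GP contributes more than the instructed 5, the largest possible value is √(4.17 × 0.83)/4.17 = 0.45, which gives DE = 1.40. An ICC of 0.46/3.17 = 0.145 would also produce 1.46, but the section says 10%.

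Two stronger readings are tempting, and the document supports neither:

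- **That the trial is underpowered.** The error runs the other way.
- **That the wrong figure will prolong recruitment.** The section on guaranteeing the targeted sample size adds GPs when enrolment is insufficient. It names no trigger and does not mention 250, 1.46 or a count of completers. The targets the text does state are 30 GPs per centre and five patients per GP.

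**Conclusion.** The point holds as an error in stated figures. A design effect of 1.46 and 250 completers cannot be obtained from 85 per arm, 60 GPs and an ICC of 0.10 at any cluster size the plan allows. The consistent figures are about 1.26 and 214 with 60 equal clusters, and at most 1.40 and 238 at a full 5 per GP.

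The direction is conservative. Under the plan's own inputs, about 255 completers give power of about 0.86, with a range of 0.84 to 0.88 across formulas, rather than 0.80. These power figures assume equal cluster sizes, the stated remission rates and no dilution of the effect. The section expects some dilution in the intention-to-treat analysis but does not quantify it, so they should not be read as the power of the primary analysis.

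How the 1.46 arose is not known. The division by one arm's GPs is only an inference, and the conclusion does not depend on it.

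**What to change.** In the Sample size section:

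1. State the number of analysed patients per GP on which the design effect is based, and say that clusters are taken as equal.
2. Correct the design effect and the required number of completers: about 1.26 and 214 if solved for 60 GPs, or 1.40 and 238 if the full 5 per GP is used as a cautious bound.
3. Restate the power at about 255 completers (design effect about 1.33, power about 0.86 by Fisher's exact test), name the formula used, and keep the statement on intention-to-treat dilution separate from it.

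This is a change of text only. The target of 300 patients, the 5 per GP and the recruitment procedure stay as they are.

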### Recruitment of participants and randomization

#### Recruitment of GPs

GP offices within a defined radius around the Freiburg and Hamburg city centers are eligible for enrollment at cluster level. Participating offices must further be listed as members of the Association of Statutory Health Insurance Physicians in the state of Baden-Württemberg or Hamburg, respectively. Specialized GPs who do not provide full primary care service, small offices with less than 400 patients per quarter, GPs offering psychotherapy, and GPs taking part in another depression trial are excluded from participation. Both study centers will recruit GPs stepwise until the targeted number of 30 GPs in each center is reached (see Figure 2).

**Figure 2 Fig2:**
[figure not shown]
**Stepwise recruitment of GPs in both study centers.** Abbreviations: GP, General Practitioner; IG, Intervention Group; CG, Control Group.

